#### Secondary outcomes

Secondary outcomes consist mainly of 16 indicators. It includes clinical and prognostic indicators (key secondary outcomes) and biochemical indicators (exploratory outcomes).

Clinical indicators include the following: (1) Average classification of the AGI grade, (2) gastric retention volume within 1 day, (3) abdominal circumference, (4) abdominal pressure, (5) frequency of bowel sounds, (6) number of days tolerating the daily feeding target, (7) proportion of patients receiving erythromycin and/or metoclopramide for feeding intolerance management, and (8) proportion of patients receiving one or more rectal laxatives for constipation management.

Biochemical indicators include the following: (1) Plasma concentration of motilin, (2) plasma concentration of gastrin, and (3) plasma concentration of prealbumin.

Prognostic indicators include the following: (1) Incidence of S-persistent inflammation, immunosuppression, and catabolism syndrome (PICS), (2) duration of invasive mechanical ventilation in days, (3) ICU length of stay in days, (4) mortality rate at day 7, and (5) mortality rate at day 28.

To assess gastrointestinal function, the AGI grade will be used (4). The AGI grade is widely used to evaluate gastrointestinal injury in patients with acute critical illness (4, 18). Evidence has shown that the AGI grading system is useful for determining the severity of gastrointestinal dysfunction/failure in sepsis (19). The specific criteria for AGI grading are provided in Supplementary File S1.

At baseline and on days 4, 8, and 10, AGI grading will be assessed, and gastric retention volume, abdominal circumference, abdominal pressure, and frequency of abdominal bowel sounds will be measured. The specific measurement procedures for these clinical indicators are detailed in Supplementary File S1. We will also record the gastric retention volume over the previous 24 h, the actual caloric intake from enteral nutrition, and any special treatments related to S-AGI, including the use of erythromycin and/or metoclopramide for feeding intolerance management or the use of one or more rectal laxatives for constipation management. In addition, we will collect venous blood samples from patients at baseline and on days 4, 8, and 10 to measure the plasma concentration of motilin and gastrin, which serve as indicators of gastrointestinal motility.

PICS was proposed by Gentile et al. to describe a series of clinical features characterized by persistent low-grade inflammation, immunosuppression, high catabolic metabolism, malnutrition, and muscle weakness in patients recovering from sepsis or severe trauma (20). Studies have shown that 43.1%–53.5% of sepsis patients develop PICS, and the mortality rate among sepsis patients with PICS is significantly higher than that among those without PICS (21). Therefore, PICS is considered a secondary trigger contributing to poor prognosis in sepsis patients (20). Based on this concept, in this trial, blood lymphocyte, serum C-reactive protein (CRP), serum albumin, and prealbumin levels on day 14 will be measured to evaluate the diagnostic criteria for PICS. At present, there are no unified standards for diagnosing PICS. Based on current literature (22, 23), PICS is defined by four criteria: ICU hospitalization ≥14 days; a continuous inflammatory response, defined as a CRP level >6 mg/L (normal range: 0–6 mg/L); immunosuppression, defined as a lymphocyte count <0.80 × 10^9^/L; and catabolism, defined as a serum albumin level <30 g/L or a prealbumin level <0.1 g/L.

In addition, the duration of invasive mechanical ventilation, ICU length of stay, mortality at day 7, mortality at day 28, and adverse events (AEs) will be recorded.

Outcome assessments will be performed by outcome assessors, who will receive standardized training in conducting interviews and performing measurements before study initiation and will follow a standard protocol. The schedule of measurements is presented in Table 1.

**Table 1 tab1:** Study schedule of the EAGISM trial.

Timepoint	D-1	D1	D2	D3	D4	D5	D6	D7	D8	D9	D10	D14	D28
Enrolment:	×												
Eligibility screen	×												
Informed consent	×												
Allocation	×												
Interventions:													
Acupuncture (EA group)													
Conventional treatment													
Assessment:													
Baseline characteristics	×												
Important medical history	×												
Sepsis complications	×												
Site of infection	×												
Special treatment	×												
Lymphocyte count	×											×	
Albumin protein	×											×	
Prealbumin protein	×											×	
Gastrin	×				×				×		×		
Gastric	×				×				×		×		
AGI grade	×				×				×		×		
Gastric retention volume	×				×				×		×		
Abdominal circumference	×				×				×		×		
Abdominal pressure	×				×				×		×		
Abdominal bowel sounds	×				×				×		×		
Total caloric intake from EN	×												
Intake of protein	×												
Use of erythromycin/metoclopramide	×												
Use of rectal laxatives	×												
Invasive mechanical ventilation	×												
Adverse events	×											×	×
PICS												×	×
ICU length of stay													
Duration of invasive mechanical ventilation													
Mortality status													

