## Introduction

### Background and rationale

Sepsis is defined as life-threatening organ dysfunction caused by a dysregulated host response to infection (1). Sepsis and septic shock are major causes of global morbidity and mortality (2), and data from high-income countries indicate that the annual incidence of sepsis is 31.5 million, with 19.4 million cases of severe sepsis contributing to 5.3 million potential deaths annually. Hospital mortality rates are reported to be 17% for sepsis and 26% for severe sepsis (3). There are limited comparable data from low- and middle-income countries, where the burden of sepsis may be even greater. Septic acute gastrointestinal injury (S-AGI) plays a key role in the initiation and progression of sepsis. Early-stage sepsis may cause intestinal barrier dysfunction, gastrointestinal motility disorder, and translocation of intestinal flora, leading to multiple organ dysfunction syndrome (MODS). Once MODS is initiated, it contributes to the development and worsening of gastrointestinal dysfunction, leading to increased hospitalization and mortality rates (4). According to existing literature, patients who were provided with preventive treatment for acute gastrointestinal injury (AGI) showed a significant increase in nutrient solution intake and a notable decrease in the duration of invasive mechanical ventilation compared to those who did not receive any preventive measures (5).

Treatments for S-AGI include early enteral nutrition, gastric motility drugs, acid inhibitors, and antimicrobial agents, which aim to protect the gastrointestinal mucosa, increase gastrointestinal motility, and improve intestinal flora (4, 6, 7). Despite the availability and application of S-AGI treatments, the case fatality rate for sepsis-3 is estimated to exceed 30%, corresponding to 700,437 deaths in China (8). Therefore, there is an urgent need to explore novel and supplemental treatments to improve clinical outcomes.

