### Statistical analysis

Statistical analysis will be performed using the SPSS software (version 29.0). For continuous data, a normality test will initially be conducted to assess distribution characteristics. If the data exhibit a normal distribution, descriptive statistics such as mean ± standard deviation (*SD*) will be used, and hypothesis testing will be carried out using a *t*-test. Conversely, if the data do not follow a normal distribution, descriptive statistics such as median and interquartile range (*IQR*) will be employed, and hypothesis testing will be performed using the *Mann–Whitney U* test. Categorical data will be described in terms of frequencies and percentages, with the chi-squared test used for hypothesis testing. The significance level for this study will be set at *α* = 0.05, with statistical significance defined as a *p*-value of <0.05. This trial includes 13 key secondary outcome indicators, covering both clinical and prognostic measures. To address multiplicity and control type I error, we applied the *Bonferroni* correction at both levels.

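### Ventilation days, ICU days and PICS incidence are compared with no account of death, so early deaths count as favourable values on three of the five prognostic key secondary outcomes

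*Protocol article*

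**What the plan says.** The section Secondary outcomes of the protocol article ranks its outcomes: "It includes clinical and prognostic indicators (key secondary outcomes) and biochemical indicators (exploratory outcomes". There are five prognostic indicators: PICS incidence, then "2) duration of invasive mechanical ventilation in days, (3) ICU length of stay in days, (4) mortality rate at day 7", and finally day-28 mortality. The two durations are raw days. No ventilator-free or ICU-free version is defined, and no value is assigned to a patient who dies.

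The same section states that "PICS is defined by four criteria: ICU hospitalization ≥14 days", with inflammatory, immune and catabolic criteria added. The laboratory part is tied to one time point: "serum albumin, and prealbumin levels on day 14 will be measured to evaluate the diagnostic criteria for PICS".

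The section Statistical analysis sets the tests by data type. Continuous data get a t-test if normal; otherwise "hypothesis testing will be performed using the *Mann–Whitney U* test". Categorical data are handled "with the chi-squared test used for hypothesis testing". A Bonferroni correction is announced, with 13 key secondary outcomes counted (8 clinical plus 5 prognostic). The Discussion adds an intention-to-treat analysis of all participants and a report of the number of, and reasons for, missing data. None of these places mentions death as an event that affects the three outcomes.

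**The concern.** A ventilated patient who dies on day 3 has a short ventilation time and a short ICU stay, and cannot meet the 14-day ICU criterion for PICS. In an all-participants comparison of raw values, that death looks like a good result three times over.

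Death will not be rare. The Introduction says of China that "the case fatality rate for sepsis-3 is estimated to exceed 30" per cent, and the Discussion describes ventilated sepsis patients as the more severe group. If electroacupuncture (EA) saved lives, the three outcomes would tend to make it look worse. If it caused early deaths, they would tend to make it look better. These are tested key secondary outcomes, so the distortion would affect results on which claims may rest.

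**Working it through.** **1. The plan's own figure.** The article gives no figure for these three outcomes. Its only calculation is the sample size for the primary outcome: n = [z(0.975)·√(2·p̄·q̄) + z(0.80)·√(p₁q₁ + p₂q₂)]² / (p₁ − p₂)². For 70% v 50%, p̄ = 0.60, so n = (1.960·√0.48 + 0.842·√0.46)² / 0.04 = 93 per group, against 94 stated. The figures of 163 and 356 for the smaller effects reproduce exactly. The sample size is not at issue; it supplies the 100 per arm used below.

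**2. PICS, by arithmetic.** Let D be the proportion dead by day 14 and q the PICS rate among patients alive at day 14, equal in both arms. Then incidence = (1 − D)·q, and the difference between arms is q times the difference in D. For q, I use the background range in the article ("Studies have shown that 43.1%–53.5% of sepsis patients develop PICS"). Values of D are assumed.

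| Dead by day 14, control v EA | PICS if q = 43.1% | PICS if q = 53.5% |
|---|---|---|
| 15% v 7% | 36.6% v 40.1% | 45.5% v 49.8% |
| 20% v 9.2% | 34.5% v 39.1% | 42.8% v 48.6% |
| 30% v 13.8% | 30.2% v 37.2% | 37.45% v 46.1% |

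EA has no effect on PICS among survivors, yet the arm with more deaths shows less PICS in every row. The gap runs from 0.431 × 8 = 3.4 to 0.535 × 16.2 = 8.7 percentage points.

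**3. Ventilation days, by simulation.** Observed duration = min(V, T). V is the ventilation time without death (log-normal, median 10 days, SD of log 0.6, identical in both arms), and T is the time of death. Each scenario used 2,000 trials of 100 per arm with a Mann–Whitney test. The 14% is 30% × (1 − 0.54) = 13.8%, rounded, from the 54% reduction in the team's cohort quoted in the Introduction. V, the mortality pairs and the timing are assumptions. The Bonferroni column uses 0.05/13 = 0.0038, one reading of the plan. Ranges reflect repeated runs.

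| Mortality, control v EA | Timing of deaths | Shift in EA median | p < 0.05 | p < 0.05/13 |
|---|---|---|---|---|
| 30% v 14% | days 1–10 | about +1 day | 25–28% | about 6% |
| 30% v 14% | days 1–28 | about +0.4 day | 7–8% | under 1% |
| 20% v 35% | days 1–10 | about −0.95 day | 21–22% | 4–5% |
| 20% v 35% | days 1–28 | not computed | 7–8% | about 1% or less |
| 30% v 25% | days 1–10 | not computed | 7.3% | not computed |
| 30% v 25% | days 1–28 | not computed | 4.8% | not computed |
| 30% v 30% | days 1–10 | none expected | 4.7% | not computed |

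**4. ICU stay, second model.** Assumed medians without death were 8–10 days of ventilation and 14–18 days in ICU; mortality was 30% v 13.8%, with no EA effect on weaning or discharge.
- Deaths concentrated early (7-day mortality about 23% v 10%): mean ICU stay 13.1 v 15.1 to 16.5 v 19.3 days, and p < 0.05 in 44–47% of trials. The control arm has the shorter mean in 95–97%.
- Deaths spread evenly over 28 days: p < 0.05 in 15–21%, and the control arm has the shorter mean in 79–86%.
- Ventilator-free days to day 28, with death scored 0, reverse the direction: 13.0 v 16.0 or 11.5 v 14.1 days, in favour of the arm with fewer deaths.

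**The case against.** **The article is condensed.** Its tests are named by data type only, and an analysis plan that is not shown may deal with death. That would carry weight if the article were merely silent. But it fixes the variable (raw days), a PICS definition that early deaths cannot meet, the tests and an all-participants analysis. Together these form a rule, and the rule gives a distorted result.

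**The size is easily overstated.** This stands. A reader might infer that about a quarter of trials would yield a false confirmatory finding. The documents do not support that: the 25–28% needs every death to fall by day 10, which no section states, and it ignores the Bonferroni correction.

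**The mortality contrast is extreme.** This also stands. A reader might take the 54% reduction as what the trial expects. It comes from a retrospective matched cohort of patients who already had S-AGI, whereas this trial excludes S-AGI at entry. The Introduction calls the mortality findings inconsistent, cites hospital mortality of 17% and 26% beside the figure above 30%, and the sample size assumes no mortality effect.

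**The remedy repeats mortality.** In these simulations EA does not affect ventilation time, so the significant ventilator-free-day results (about 48% of trials at 30% v 14%) reflect mortality alone, already two of the five prognostic outcomes. That is a true cost, and competing-risk analysis is an equally valid choice.

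**Mortality is reported alongside.** A conflict would be visible, but the three comparisons would remain uncorrected.

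**Conclusion.** The point holds as a directional bias: other things equal, the arm with more deaths before extubation, ICU discharge or day 14 looks better on ventilation days, ICU days and PICS. It arises only if mortality differs between arms, weakens as deaths come later, and could be offset by a real effect on weaning.

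The distorted estimate matters more than the rate of formal false claims. For ventilation that rate runs from near nominal (30% v 25% mortality) to about a quarter at 0.05 (30% v 14%, all deaths by day 10), and to about 6% at 0.05/13 in that same scenario. ICU stay is the more exposed outcome in the second model, but was examined only at 0.05.

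A reader might also infer that the plan is tilted towards EA. It is not: if EA lowers mortality, the bias runs against it. The primary outcome is outside this point. The plan should be changed, but the trial's main conclusion does not depend on it.

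**What to change.** In Secondary outcomes and the abstract, replace the tested durations with ventilator-free days and ICU-free days to day 28, with death by day 28 scored as 0 or worst rank, compared by Mann–Whitney with a confidence interval. A competing-risk analysis, with death as the competing event, is an acceptable alternative. Replace PICS incidence as the tested outcome with PICS or death by day 14. Report mortality, PICS alone and the raw durations by survivor status beside these, as description only, because restricting to survivors conditions on an event after randomisation.

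Cost: the text says that ventilation duration, ICU stay and day-28 mortality are already recorded, and evaluation runs to day 28. No new visits should be needed, though the case report form should be checked for the relevant dates. The free-day outcomes and the composite partly repeat mortality, so the components must be shown. The trial is registered, so the secondary outcomes in the registration need a dated update.

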### Safety assessment

While generally regarded as a safe therapeutic method with minimal risk of adverse effects (24), any adverse events (AEs) that occur during the study will be carefully evaluated, promptly addressed, and thoroughly recorded in the case report form (CRF). Adverse effects such as needle breakage, localized hematoma formation, bleeding, or severe local discomfort will be specifically attributed to the use of acupuncture, whereas those resulting from chemical or surgical interventions will not be considered related to acupuncture therapy. In the case of any serious adverse event (SAE) occurring in either group, it will be promptly reported to an independent ethics committee for thorough evaluation. This distinguished ethics committee is also responsible for conducting annual follow-up assessments of this research project.

### Quality control

To ensure study consistency, comprehensive training will be provided by the principal investigator (JX) to research staff regarding the study protocol, acupuncture manipulation techniques, outcome assessment methods, and participant follow-up procedures. Furthermore, it is important that a single research assistant or outcome assessor assumes responsibility for evaluating gastrointestinal function throughout the entire trial. Assessors will promptly collect and review all forms during each visit for outcome assessment and record the data in the CRF.

### Data management

The collected data will first be documented in the CRF by clinical research coordinators, then thoroughly reviewed by two trained clinical research associates, and finally entered into the EpiData software by a trained research assistant. This rigorous protocol ensures the utmost accuracy, authenticity, and traceability of the data. Furthermore, an independent data monitoring committee will be established to oversee and manage the quality of the data, ensuring complete impartiality without any conflicts of interest with the researchers or sponsors.

### Sample size

A parallel-design, randomized controlled trial methodology will be employed in the trial, with the primary outcome measure being the incidence of S-AGI. Based on clinical observations, the estimated incidence of S-AGI in the conventional treatment group is 70%. It is anticipated that electroacupuncture can potentially reduce the occurrence rate of S-AGI to 50%. With a significance level (*α*) of 0.05 and a power of 0.8, the sample size calculation yielded 94 participants per group. To account for potential loss to follow-up, we plan to include a total of 200 sepsis patients, with 100 patients allocated to each group. To account for uncertainties and maintain adequate power if the effect size is smaller than expected, sample sizes were also calculated as 163 participants per group for a 15% effect size and 356 participants per group for a 10% effect size.

### Statistical analysis

Statistical analysis will be performed using the SPSS software (version 29.0). For continuous data, a normality test will initially be conducted to assess distribution characteristics. If the data exhibit a normal distribution, descriptive statistics such as mean ± standard deviation (*SD*) will be used, and hypothesis testing will be carried out using a *t*-test. Conversely, if the data do not follow a normal distribution, descriptive statistics such as median and interquartile range (*IQR*) will be employed, and hypothesis testing will be performed using the *Mann–Whitney U* test. Categorical data will be described in terms of frequencies and percentages, with the chi-squared test used for hypothesis testing. The significance level for this study will be set at *α* = 0.05, with statistical significance defined as a *p*-value of <0.05. This trial includes 13 key secondary outcome indicators, covering both clinical and prognostic measures. To address multiplicity and control type I error, we applied the *Bonferroni* correction at both levels.

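### Continuous gastrointestinal outcomes measured at baseline and on days 4, 8 and 10 are assigned only a two-sample test picked by a normality test, with no baseline term or visit named; a baseline-adjusted analysis would be more precise at almost no cost

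*Protocol article*

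**What the plan says.** The Secondary outcomes section sets a repeated schedule for the clinical measures: "At baseline and on days 4, 8, and 10, AGI grading will be assessed, and gastric retention volume, abdominal circumference, abdominal pressure" and bowel sounds are all recorded at those four times. The hormones follow the same schedule; the investigators will "collect venous blood samples from patients at baseline and on days 4, 8, and 10 to measure the plasma concentration of motilin and gastrin".

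The Statistical analysis section gives one rule for all continuous data. It begins with "For continuous data, a normality test will initially be conducted to assess distribution characteristics". If the data look normal, "hypothesis testing will be carried out using a *t*-test"; if not, "hypothesis testing will be performed using the *Mann–Whitney U* test". It names no baseline covariate, change score, repeated-measures method or visit at which the groups are compared.

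The same section counts 13 key secondary outcomes and applies a Bonferroni correction. The Secondary outcomes section lists 8 clinical and 5 prognostic indicators as key (8 + 5 = 13) and classes the biochemical indicators as exploratory.

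**The concern.** The stated method does not match the stated design. Each of the six outcomes has a baseline value and three later values, but the only test named is one that compares two independent sets of numbers.

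Two things follow. First, a test without a baseline term leaves between-patient variation in the error that a baseline covariate could remove. This costs most where the threshold is strict, as it is for the key secondary outcomes after Bonferroni. Second, the normality test decides whether means or ranks are compared. With no visit fixed, day 4 of an outcome could be reported as a difference in means and day 8 of the same outcome as a shift in ranks, and the two results could not be read together.

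**Working it through.** **The plan's own figure.** The article gives no precision or power figure for continuous outcomes. Its only calculation is for the binary primary outcome, 70% against 50%: "With a significance level (*α*) of 0.05 and a power of 0.8, the sample size calculation yielded 94 participants per group". The two-sided pooled-variance formula is

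n = [1.96·√(2·p̄·(1−p̄)) + 0.842·√(p₁(1−p₁) + p₂(1−p₂))]² / (p₁−p₂)².

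| Difference | Recomputed per group | Stated per group |
|---|---|---|
| 70% vs 50% | 93 | 94 |
| 70% vs 55% | 163 | 163 |
| 70% vs 60% | 356 | 356 |

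Using the pooled variance in both terms gives 94.2 for the first row. The figures reproduce, and nothing below changes them.

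**Inputs for the continuous outcomes.** From the article: 100 patients per arm, α = 0.05, 13 key secondary outcomes with Bonferroni. Assumed: two-sided tests; one test per key secondary outcome, so the threshold is 0.05/13 = 0.00385; a true difference of 0.4 SD; correlation r between baseline and follow-up of 0.3, 0.5 or 0.7. No correlation is given in the document.

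**Variance at one visit.** Relative to an unadjusted comparison of raw values, analysis of covariance on baseline has variance 1 − r².

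**Power.** With d = 0.4 and n = 100, the standardised effect is 0.4/√(2/100) = 2.83 unadjusted, and 2.83/√(1 − r²) adjusted. The two-sided critical value at 0.00385 is about 2.89, so power = Φ(effect − 2.89).

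**Detectable difference at 80% power.** (2.89 + 0.842)·√(2/100) = 0.53 SD unadjusted, multiplied by √(1 − r²) when adjusted.

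| Analysis at one visit | Relative variance | Reduction | Power for 0.4 SD | Detectable difference |
|---|---|---|---|---|
| Unadjusted | 1.00 | – | 48% | 0.53 SD |
| Adjusted, r = 0.3 | 0.91 | 9% | 53% | 0.50 SD |
| Adjusted, r = 0.5 | 0.75 | 25% | 65% | 0.46 SD |
| Adjusted, r = 0.7 | 0.51 | 49% | 86% | 0.38 SD |

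**Which outcomes the threshold covers.** Gastric retention, abdominal circumference, abdominal pressure and bowel sounds are among the 13. Motilin and gastrin are exploratory: the variance column applies to them, but the power and detectable-difference columns do not.

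**Does the normality test distort error rates?** In 10,000 simulated trials per distribution, with 100 per arm and a nominal 0.05, the two-stage procedure rejected a true null in 5.0% to 5.4% of trials for normal, gamma and lognormal data. The Mann–Whitney branch was taken in about 10% of trials with normal data, 43% and 92% with two gamma shapes, and all trials with lognormal data. Error control is therefore barely affected, but the branch taken, and with it the effect measure, does depend on the data.

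**The case against.** **This is detail for the analysis plan.** The source is a journal article with a one-paragraph statistics section, and a fuller plan may exist. Covariates and visits for secondary outcomes are often settled there, so their absence alone would be no finding. What stands is that the article does not stay silent: it fixes the test and the rule for choosing it for all continuous data, and a better rule is available from data already scheduled.

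**The tests are valid.** This is correct. Under randomisation an unadjusted comparison is unbiased on average, and chance baseline imbalance is already reflected in its standard error. The point is efficiency and clarity, not bias.

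**Stronger readings that the document does not support.**

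- *Most of the available precision is lost.* No correlation is given, and a single-visit adjustment removes more than half the variance only if r exceeds about 0.71. Reductions of 56%, 58% and 69% (r = 0.3, 0.5, 0.7) appear only when one unadjusted visit is compared with a baseline-adjusted mean of three visits, with relative variance (1 + 2r)/3 − r² under equal correlations. That mean is a different estimand.
- *The baseline values are discarded.* The article does not say whether raw values, changes or averages are tested. A t-test on change is compatible with its text. Change has relative variance 2 − 2r, so adjustment would then save 1 − (1 + r)/2, that is 35%, 25% and 15% at the same correlations. The gain has a different size but does not vanish.
- *AGI grade would gain too.* Patients meeting any AGI standard are excluded, so its baseline does not vary. The same criterion may narrow the baseline range of gastric retention and abdominal pressure and pull r towards the lower end.

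**Conclusion.** The point holds as a weakness of specification in secondary and exploratory analyses. For six repeatedly measured outcomes, the article commits to a test chosen by a normality test, without stating how baseline is used or which visit is compared. No result would be invalid, and the primary outcome and its sample size stand.

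The size depends on the correlation, which must be assumed. At r = 0.3 the gain is small (five points of power); at r = 0.7 it is large (38 points). These power figures compare adjustment with a raw-value test at one visit, and assume 100 evaluable patients per arm and one test per key secondary outcome. Missing values or a larger Bonferroni divisor would lower power in every row of the table. The change is worth making because it needs no new data.

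**What to change.** For gastric retention, abdominal circumference, abdominal pressure, bowel sounds, motilin and gastrin, replace the normality-test rule with one prespecified baseline-adjusted analysis per outcome, and do so before any comparison by group:

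- Either analysis of covariance at the named visit with the baseline value as covariate, or a linear mixed model with treatment, day, treatment-by-day and baseline value.
- One contrast per outcome named in advance, for example day 8, the first scheduled assessment after the 7-day treatment period. Other visits are descriptive.
- The scale of analysis fixed in advance. Gastric volumes can be zero, so a plain logarithm will fail; choose a transformation that allows zeros.
- A statement of how values missing because of death are handled. The Introduction cites a sepsis case fatality above 30%, and 7-day mortality is itself an outcome, so some day-8 and day-10 values will not exist. A mixed model retains patients' earlier values but does not settle what a value after death means.

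The cost is a revision of the analysis text, slightly more analysis work and reliance on a model assumption. The baseline measurements are already scheduled, and the named software can fit these models.
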